Despite the contribution in elucidating important mechanisms in chronobiology, the majority of the studies do not account for differences of circadian rhythmicity among individuals. Distinct chronotypes reflect different timings of circadian behavior, physiology, and even patterns of clock genes expression. Besides regulating sleep, the chronotype can have a major influence on appetite. Thus, the characterization of individual chronotypes (expression of circadian rhythmicity), as part of a patient phenotype, is gaining increasing importance for the development of novel and pinpointed nutritional interventions. A randomized clinical trial showed that a chronotype-adjusted diet was more effective than the traditional hypocaloric diet in the improvement of anthropometrical parameters in patients with obesity (36). Individual circadian variations may be valuable, and a critical first step, for providing information to design therapeutic strategies and to help “fine-tune” chronobiology interventions, including chrononutrition approaches (37). Research in this field is currently hindered by the fact that only a few studies assessed simultaneously the chronotype and nutrient intake and timing during the interventions. Furthermore, there is no standard method to objectively define chronotypes. Usually, this is determined by a combination of questionnaires, evaluation of clock genes expression and/or protein levels, determination of non-invasive clock outputs, such as core body temperature, and heterogeneous pools of biomarkers that act as readouts of the intrinsic circadian rhythms (38–41). Although there is an increasing interest in chronotype, as a novel dimension of nutrition and health, there is still a lack of consistent evidence regarding its relation to obesity and metabolic disturbances (42, 43). Researchers in this field highlight the need for more research and proper characterization of clock gene expression and circadian biomarkers in obesity. Furthermore, most studies have a high risk of bias and do not evaluate parameters related to metabolic dysfunction such as adiponectin, leptin, and insulin (42, 44).

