#### Dietary intake assessments

2.5.4.

Dietary intake will be assessed using two methodologies: a 3-day food diary included in the NutriClock app (53) and a Food Frequency Questionnaire (FFQ). To ensure equal access and opportunity to participate in the research study, regardless of the socioeconomic level, availability of a smartphone, and/or ability to use it, participants can opt to complete the 3-day food diary in the traditional pen-and-paper format.

The participants will start filling out the 3-day food diary on the day of their visit to the research center to collect biological samples (Visit 2, Figure 1). All foods, including drinks, beverages, and dietary supplements consumed during the 3 days should be registered. Participants will also be required to register the meal time and type (breakfast, lunch, dinner or snack). Food portions will be estimated using either a photographic method (participants can take a picture of their meal through the mobile application), using the weight or volume, pre-determined household measures, and/or default mean portions where the participants cannot quantify a specific food item.

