The conversion of food into energy and nutrients will be based on the Portuguese Food Composition Table (54), incorporated into the app and, if necessary, other food composition tables. In the app’s food diary section, participants can also upload pictures of the nutritional information/food labeling of the food items being consumed, if available. In the backoffice, it is possible to continuously adapt and complete the information on the Portuguese Food Composition Table by adding nutritional information for new food items or meals. The Portuguese Food Frequency Questionnaire (FFQ) is a validated semi-quantitative instrument that assesses dietary intake, reporting the previous 12 months. This tool will be used to collect information on the consumption of less frequently eaten foods and, therefore, minimize interferences with the day-to-day variation of food intake (55). The Portuguese FFQ includes a pre-determined list of 86 food items or groups, and nine frequency categories ranging from “Never or less < 1 per month” to “6+ per day” (56). Food consumption is quantified by multiplying the reported intake frequency by the food item or group average standard portion, and by a seasonal variation factor for items consumed only in a specific season. The conversion to nutrients will be supported by a compilation of databases on the nutritional food composition, including the Portuguese Food Composition Table (54).

The data collected with the FFQ will be mainly used to perform a global characterization of the participants’ dietary intake in the previous 12 months. The data collected using the 3-day food diary will be used to correlate dietary intake and circadian biomarkers.

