### Statistical analysis

2.6.

Statistical analysis will be performed using the IBM SPSS Statistics software version 28.0.1. (IBM Corp., Warrington, United Kingdom) and GraphPad Prism version 8 (GraphPad Software, Inc.; San Diego, United States). Continuous variables will be presented as the mean ± standard deviation (SD), median, and interquartile range [Q1–Q3]. Categorical variables will be presented in frequency and percentage. The normality of continuous variables will be tested using the Shapiro–Wilk test if *n* < 50 or the Kolmogorov–Smirnov test if *n* ≥ 50. Parametric tests (Independent Sample *t*-test) will be used to compare the differences between the study and the control groups if the data has a normal distribution, otherwise, non-parametric tests (Mann–Whitney *U*-tests) will be performed. According to the normality or non-normality of data distribution, Spearman’s rank-order correlation (ρ) or Pearson’s correlation coefficient (r) will be performed to calculate and assess the strength of correlations between the study variables. Statistical significance will be set at *p* < 0.05.

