Circadian oscillations of gene expression also regulate whole-body metabolism (72). For example, Gaspar et al. showed that patients with obstructive sleep apnea, which is strongly related to obesity (73, 74), have different patterns of clock gene expression compared with healthy individuals (51), further highlighting the importance of assessing the circadian features in disease.

The importance of determining the circadian rhythm has been extensively reported; although it started more focused on pharmacological studies (40), this relevance has extended to nutrition. From this, the concept of chrononutrition emerged, mostly because peripheral circadian clocks are mainly synchronized by food intake (24, 31). Furthermore, the circadian clock also regulates nutrient challenges, through transcription factors that modulate the expression of genes with regulatory roles in nutrient pathways (37, 75) Therefore, there is the potential to improve metabolic homeostasis by coordinating behavioral changes with the body’s daily rhythm. The identification of genetic patterns and signatures in response to dietary intake may guide the advance of new therapeutic approaches.

Designing dietary interventions that account for the quality, quantity and timing of food intake could be an approach to modulate the circadian rhythm and clock-controlled genes and optimize the synchronization of central and peripheral clocks, with a positive impact on overall metabolism. Therefore, the characterization of circadian and dietary makers is a critical first step to underpin therapeutic strategies and to support the adjustment of chrononutritional approaches for the management of chronic diseases such as obesity. In the present study, caloric intake, macronutrients (proteins, carbohydrates, and lipids), and meal times (time of the first meal of the day, time of last meal of the day and overnight fasting period) will be evaluated, in order to assess the impact of dietary intake (timing and nutrients) on circadian rhythm markers.

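### Unadjusted correlations of first- and last-meal clock time with clock genes can reflect circadian phase alone, so they cannot show an impact of meal timing

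*Protocol article*

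**What the plan says.** All references are to the protocol article.

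- **Exposure.** Section 3 (Discussion) lists the meal-timing variables: "time of the first meal of the day, time of last meal of the day and overnight fasting period". The first two are clock times and the third is a duration.
- **Aim.** The same sentence says that they are evaluated "in order to assess the impact of dietary intake (timing and nutrients) on circadian rhythm markers".
- **Data.** Under section 2.5.4, the time and type of each meal are recorded for three days, and "The data collected using the 3-day food diary will be used to correlate dietary intake and circadian biomarkers".
- **Test.** Under section 2.6, a Pearson or Spearman coefficient "will be performed to calculate and assess the strength of correlations between the study variables", with a threshold of p < 0.05. No covariate, partial correlation or regression is named.
- **Outcome timing.** Under section 2.5.2, blood for the clock genes is drawn at 08:00 and 16:30 for every participant.
- **Chronotype.** Under section 2.5.5, the Munich Chronotype Questionnaire yields MSFsc, a local clock time.
- **Premise.** The Introduction says: "Distinct chronotypes reflect different timings of circadian behavior, physiology, and even patterns of clock genes expression".

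**The concern.** The exposure, the test and the aim are all stated, and they do not fit together. A person with a later circadian phase tends to sleep, wake and eat later by the clock. On the Introduction's premise, that person may also be at a different point of the clock-gene cycle when blood is taken at a fixed hour. Phase is then a common cause of meal clock time and of the measured gene level. A two-variable correlation cannot separate an effect of eating from this shared cause.

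The article hopes to inform chrononutrition interventions. If a phase artefact were read as an impact of meal timing, it could be taken forward as a dietary target. The limitations in the Discussion do not mention this.

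**Working it through.** **Plan's own figure.** The article gives no number for the meal-timing analysis; only its sample size enters here. Section 2.3: (0.18×0.82 + 0.55×0.45) × (1.96 + 0.84)² / (0.55 − 0.18)² = 0.3951 × 7.84 / 0.1369 = 22.63, so 23 per group and 46 in total, as stated. The check uses N = 46 and the stated inflated total of 64.

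**Assumptions (the article gives none of these).** MSFsc, written C, has SD 1 h. Sleep duration D has SD 1 h. Diary-day sleep moves s = 0.5 or 1.0 h per hour of C. The lag between sleep and meal has SD L = 1.0 or 1.5 h and is independent of C. The gene level G at the sampling hour has correlation ρ = 0, 0.3 or 0.5 with C. Eating has no effect on G.

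**Formulas.** First meal M = sC + D/2 + lag, so

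r(M,C) = s / √(s² + 0.25 + L²), and r(M,G) = ρ × r(M,C).

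For s = 1 and L = 1: r(M,C) = 1/√2.25 = 0.67, and with ρ = 0.3, r(M,G) = 0.20.

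**Results.** Rejection rates for first-meal clock time against the gene come from 20,000 simulated studies per scenario (two-sided Pearson test at 0.05):

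| s | L | r(M,C) | r(M,G), ρ = 0.3 / 0.5 | N = 46, ρ = 0.3 / 0.5 | N = 64, ρ = 0.3 / 0.5 |
|---|---|---|---|---|---|
| 1.0 | 1.0 | 0.67 | 0.20 / 0.33 | 26.6% / 62.7% | 35.9% / 77.9% |
| 1.0 | 1.5 | 0.53 | 0.16 / 0.27 | 18.4% / 44.0% | 24.7% / 57.5% |
| 0.5 | 1.0 | 0.41 | 0.12 / 0.20 | 12.4% / 27.5% | 16.9% / 36.9% |
| 0.5 | 1.5 | 0.30 | 0.09 / 0.15 | 9.0% / 17.2% | 10.7% / 22.2% |

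Last-meal time gives the same rates to within one percentage point. With ρ = 0, rejection is 4.7% to 5.4%.

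**Overnight fast.** First meal minus last meal removes the term sC when chronotype moves both ends equally. Mean r is about 0 and rejection is 4.6% to 5.3%, against chronotype and gene alike.

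**Adjustment for MSFsc.** The numerator of the partial correlation is r(M,G) − r(M,C)·r(G,C) = ρ·r(M,C) − r(M,C)·ρ = 0. In the simulation it rejects in 4.6% to 5.3% of studies.

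**Wake-to-first-meal interval.** Against the gene this also rejects at 4.7% to 5.4%, but only because the lag was assumed independent of chronotype. If meals are instead anchored to the clock, the interval is M minus wake time with M unrelated to C. Its correlation with C is then −s / √(s² + 0.25 + L²), that is −0.30 to −0.67: the same size with the opposite sign.

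**The case against.** The strongest case on the other side has five parts.

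- **The article is condensed.** It states no sleep-relative variable and no adjustment, but rules out neither. A reader might infer that meal timing is never set against the person's own sleep. The text does not support *never*; a fuller plan may cover it. What stands is that the exposure, test and aim that are stated do not match.
- **Meal time against chronotype is itself an aim.** The Objective and the end of the Introduction ask how chronotype relates to diet. If late types eat later, that is a true finding. This stands: the r(M,C) values above are not errors. Only the path from meal time to biomarker can mislead.
- **The size is unknown.** A reader might infer that late eating follows from late chronotype by construction, so that a significant gene correlation is to be expected. The documents do not support this. Section 1 asserts a chronotype–gene link without a size, and with no link the test keeps its 5% level. Also, the diary starts on the day of the 08:00 fasting draw, so that day's first meal is partly set by the visit, which may weaken the tie to chronotype.
- **Overnight fast and intake after midnight.** A reader might extend the criticism to the overnight fast, or suppose that a snack after midnight counts as the next day's first meal. The first is a duration, in which an equal shift cancels. For the second, the article nowhere defines the day as a calendar day.
- **The causal aim rests on one word.** Section 2.5.4 and the conclusion speak of correlating and associating. This is fair, and it makes the wording easy to repair, but the Discussion sentence does state impact as the purpose.

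**Conclusion.** The point holds in limited form. It concerns first- and last-meal clock time against circadian biomarkers, tested by unadjusted correlation and read as impact. With no effect of eating, rejection at the 5% level is about 5% when the gene level at sampling is unrelated to chronotype, about 9% to 36% when that correlation is 0.3, and about 17% to 78% when it is 0.5. These ranges rest on the assumed SDs, slopes and correlations above; the article supplies only the sample sizes, the fixed sampling hours and the direction of the premise. A significant correlation would therefore not by itself show an effect of meal timing. It does not follow that the diet-timing question is unanswerable, because MSFsc is already collected and can be adjusted for.

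**What to change.** In section 2.6, state that correlations of first- and last-meal clock time with circadian biomarkers will be reported as partial correlations controlling for MSFsc (on ranks where Spearman would be used), alongside the unadjusted ones. In the Discussion sentence on dietary variables, replace impact with association.

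Intervals from waking to first intake and from last intake to sleep onset may be added as a sensitivity analysis where diary-day sleep times exist. The sleep diary is mentioned only in the Discussion as an app component, and the pen-and-paper option in section 2.5.4 covers only the food diary, so these times may be incomplete. The intervals should not replace clock times, because they carry the opposite correlation with chronotype when meals are anchored to the clock.

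Cost: a sentence or two, with no new data for the main change and no change in sample size. Each partial correlation uses one degree of freedom (43 instead of 44 at N = 46). Error in self-reported MSFsc leaves some residual confounding. If meal timing itself shifts MSFsc, the partial correlation over-adjusts somewhat, which is a reason to show both versions. The simulation used Pearson coefficients; the rank version was not simulated.

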## Ethics and dissemination

4.

This is a research project that falls under the scope of Portuguese Law no. 21/2014 April 16 that covers all research with humans, including observational studies. This study will be carried out on adults over the age of 18 years. Adults who are unable to provide their informed consent will not be included in the study.

The research project was approved by the Ethics Committee of the Centre’s Regional Health Administration (ARS Centro) on 29th January 2021 (Proc no. 67-2020). The research will be carried out in strict compliance with the ethical principles of the Helsinki Declaration and obeying international, European, and national legislation, including the General Data Protection Regulation (Regulation (EU) 2016/679). The principles of autonomy, nonmaleficence and beneficence, fairness, and clear informed consent will be strictly respected. The researcher will assure that the informed consent document will be available to the volunteers before starting any procedure of the study. The recruitment will be gender-independent to minimize gender bias.

Biological samples will be protected by the principle of non-commercialization, commercial use, patenting, or any financial gain, and the principle of the non-susceptibility of patenting human genetic heritage. The samples will be used exclusively to support this research initiative and will be destroyed immediately after use.

The participants will not be identified by any of their data, to ensure the confidentiality and anonymity of the collected data, a unique ID number will be assigned to each participant. Only the Principal Investigator will have access to the list with the match between the participant’s ID and their data. This list will be in electronic format, with restricted access to its content and secured with a password, preventing confidential information from being accessed, printed, forwarded, or copied by an unauthorized person(s). Personal data collected in the context of this study, and shared between team members, will be kept in secure files, with restricted access, be they electronic or physical, and kept after the conclusion of this study, for the time defined by law.

Participants have the right to withdraw from the study at any time, without the need to provide a reason, if they wish not to do so. Participants will be assured that if they wish to withdraw from the study, their medical care will not be affected. Except if the participant indicates otherwise, any data collected up to the point of withdrawing consent will be included in the final analysis.

The results will be disseminated in group data, and individual results that might identify the participant will never be shown to the public. The results and deliverables of this research project will be available in academic health-related publications and through presentations in international scientific meetings.

## Data availability statement

The original contributions presented in the study are included in the article/supplementary material, further inquiries can be directed to the corresponding author.

## Ethics statement

The studies involving human participants were reviewed and approved by the Ethics Committee of the Centre’s Regional Health Administration. The patients/participants provided their written informed consent to participate in this study.

